**Methods:**

We will use diethylhexyl phthalate (DEHP), a major indoor air pollutant, as a model SVOC in this novel protocol. The Swiss official Commission on Ethics in Human Research, Canton de Vaud, approved the study on October 14, 2020 (project-ID 2020-01095). Participants (n=10) will be repeatedly exposed (2 short daily exposures over 4 days) to isotope-labeled DEHP (DEHP-d4) to distinguish administered exposures from background exposures. DEHP-d4 aerosols will be generated with a small, portable, aerosol-generating device. Participants will inhale DEHP-d4-containing aerosols themselves with this device at home. Air concentrations of the airborne phthalates will be less than or equal to their occupational exposure limit (OEL). DEHP-d4 and its metabolites will be quantified in urine and blood before, during, and after exposure.

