#### Aerosol Generation and Vaping Machine

To adapt the ENDS to generate DEHP aerosols at controlled concentrations, we used a vaping machine that was developed in the Unisanté laboratory in collaboration with the University Centre of Legal Medicine of Lausanne (CURML) [46]. The purpose of the vaping machine was to replicate the puffing behavior of an individual using an ENDS according to the method n°81 recommended by the Cooperation Centre for Scientific Research Relative to Tobacco (CORESTA) [47]. This method describes the requirements for the generation and collection of e-cigarette aerosols for analytical testing purposes and led to an ISO (International Organization for Standardization) standard (20768:2018). Our vaping machine included 3 ports, each for an ENDS head (e-liquid tank, atomizer, and mouthpiece), a power supply, a piston syringe, a pinch-valve system, and silicon tubing (Figure 2). The machine was equipped with its own power supply, which replaced the individual ENDS batteries. This provided a steady-state power of 12 W throughout all experiments. The replacement of the ENDS battery by the machine’s power supply precisely controlled puff duration during the experiments. The piston, in combination with the pinch valve system, controlled the puff volume, that is, the volume leaving the ENDS. Puff volumes were trapped by n-hexane in subsequent glass impingers (with P1 porosity fritted nozzle tip, joint connection NS 29/32, Bistabil, Sigma Aldrich) for analytical analysis. Puff duration (3 seconds per puff), volume (55 mL per puff), and frequency (30 second between puffs) were set up as per CORESTA criteria. Tests were carried out in triplicates. Control tests served to verify that the entire setup was not contaminated by DEHP-d4. A total of 3 ENDS with 0.8-ohm atomizers were used for all the experiments. New atomizers were used in each experiment.

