#### Participant Exposure

Participants will use the portable aerosol-forming device themselves, first in our facilities (day 1) and then at home (days 1-4). The e-liquid will have a PG/VG ratio of 50/50 with 1% (w/w) ethanol and 0.02% (w/w) DEHP-d4. The participants enrolled in the study will press a button on the ENDS battery. The coil will heat the e-liquid, generating an aerosol with DEHP concentrations less than or equal to the OEL.

The e-liquid will be prepared in advance for DEHP-d4 quantification analysis and will be stored at room temperature during the exposure week. A fraction of the e-liquid will be sent to the analytical laboratory of EPFL to confirm the DEHP-d4 concentration in the e-liquid, and the rest will be frozen at –20 °C until use. On the day of the first exposure to DEHP, the e-liquid will be defrosted. A vial with a weighted amount of e-liquid sufficient for 1-week exposure (ie, reserve) will be prepared for each participant. This vial will be stored at room temperature at the participant’s place, where they will use it to refill the ENDS e-liquid tank when needed. Therefore, a stability test is required to verify DEHP-d4 concentration after several days of storage at room temperature. This step is also important for the relevance of the study. On day 5, the participant will return the ENDS and the e-liquid vial, which will be weighed to calculate the exact amount of e-liquid puffed by the participant, hence the amount of puffed DEHP-d4.

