### Part I: Dosing Protocol

#### E-Liquid Formulation and Testing Conditions Optimization

The optimized e-liquid formulation had a PG/VG ratio of 50/50 with 1% (w/w) ethanol and 0.02% (w/w) DEHP-d4. Ethanol was necessary to dissolve DEHP-d4 and then create a homogeneous solution with PG/VG. The mean recovery in impingers was 89% (SD 5%) of the mass of aerosolized DEHP-d4 (n=5). The optimized number of impingers, impinger volume, and n-hexane volume in each impinger were 3 mL, 125 mL, and 80 mL, respectively. The number of puffs per experiment (n=36) was set to produce 2 dm^3^ of aerosol, a volume that generated quantifiable amounts of DEHP-d4, and that was a submultiple of 1 m^3^ (the volume used to define the OEL), which simplified calculations.

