#### DEHP-d4 Mass Balance and Aerosol Concentrations

Total DEHP-d4 mass mean recovery for e-liquids, ENDS heads, and impingers was 100% (SD 22%; n=4). A DEHP-d4 concentration of 0.02% (w/w) in the e-liquid was confirmed by chemical analysis and produced aerosols containing 25.4 (SD 3.4) mg/m^3^ DEHP-d4 (median 26 mg/m^3^), corresponding to a mean of 1.4 (SD 0.2) μg DEHP-d4 per puff (n=6).

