## Discussion

We developed a method to generate aerosols containing controlled concentrations of SVOCs of toxicological relevance (ie, DEHP in this study) for controlled human exposure studies. Aerosols were generated by a portable and easy-to-use device (ENDS). Our results showed that DEHP in the e-liquid was stable for the duration of the study and that ENDS-generated aerosol particles were in the respirable range. Therefore, DEHP was likely to reach the alveoli, be absorbed, and enter the systemic circulation. Knowledge of human toxicokinetics after SVOC aerosol inhalation exposures will help regulatory agencies set new exposure limits and new requirements for toxicity reporting from manufacturers or suppliers because the data are human data instead of animal data. Some e-liquid leaking occurred with our first participant. This will be prevented by asking the next participants to keep the ENDS at home in a vertical position.

In the near future, our portable aerosol device will be used to study biomarkers of phthalate exposure in humans and the influence of these chemicals on a panel of readouts related to human health. We believe that this protocol with a take-home device has an easy approach, and we therefore anticipate that participant compliance rates to the exposure protocol will be high. The potential limitations of this protocol are the risks of missing part of the dose in blood and urine because only DEHP metabolites, not the parent compound, are quantified in these fluids, and participants are asked for spot urine samples, not 24-hour urine collection for every day of exposure. We hope this protocol will help other researchers design human inhalation studies of environmental substances that can contribute to the large data gap that exists today.

The results of this study will add new and important human data on the toxicokinetics of SVOCs such as DEHP upon repeated, inhalation-only exposures. Understanding phthalate toxicokinetics upon repeated exposure will help researchers understand possible phthalate accumulation in the body (if any) and improve models estimating internal exposures from external exposures, as well as interpret biomonitoring results from the general population, where urine is often collected at different times.

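### The day-5 weighing is called the exact dose puffed, but it counts leaked liquid as inhaled and gives one total for eight exposures

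*Protocol article*

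**What the plan says.** Under Participant Exposure, each participant receives a reserve of e-liquid: "A vial with a weighted amount of e-liquid sufficient for 1-week exposure (ie, reserve) will be prepared for each participant". The vial is kept at room temperature at the participant's home and is used to refill the tank. Device and vial both come back to the study team after the last exposure day, and the dose is derived from them as follows: "which will be weighed to calculate the exact amount of e-liquid puffed by the participant, hence the amount of puffed DEHP-d4". The abstract gives the regimen as "2 short daily exposures over 4 days", which is eight exposures. Only the first takes place under supervision.

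The Discussion reports: "Some e-liquid leaking occurred with our first participant". The remedy stated there is to ask later participants to keep the device upright at home. The article describes no measurement of leaked liquid and no handling of the first participant's dose.

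Under DEHP-d4 Stability in E-Liquid (Results), concentration fell by about 10% at room temperature. The authors attribute this to wall adsorption or to analytical error, and conclude stability for storage at –20 °C.

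**The concern.** The article fixes a rule: mass lost equals liquid puffed, and liquid puffed gives DEHP-d4 puffed. Three things stand between the balance reading and an exact dose.

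- **Leakage.** Leaked liquid is missing from the balance just as puffed liquid is. The article reports that this happened in the first person studied. Upright storage at home does not cover the journeys from the facility on day 1, to and from the day-3 visit if the device is carried, and back on day 5.
- **Concentration.** The step from liquid to DEHP-d4 assumes the nominal 0.02% held all week at room temperature.
- **Timing.** One weight difference is one total. It does not say how much was taken at each of the eight exposures.

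The administered dose is the denominator of any absorbed or excreted fraction. It is also the external side of the Discussion's aim to improve models that estimate internal from external exposure. An overstated dose makes such fractions too small. Leakage differs from person to person, so with at most 10 participants it can also pass for a difference between people. The Discussion's limitations cover dose missed in blood and urine, but not error in the dose administered.

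**Working it through.** **Inputs from the article**
- Aerosol concentration 25.4 (SD 3.4) mg/m³ and 1.4 (SD 0.2) µg per puff (DEHP-d4 Mass Balance and Aerosol Concentrations, Results)
- Puff volume 55 mL (Aerosol Generation and Vaping Machine)
- DEHP-d4 in e-liquid 0.02% w/w, i.e. 0.0002 (Participant Exposure)
- Exposures 2 × 4 = 8 (abstract, Methods)
- Room-temperature loss about 10% (DEHP-d4 Stability in E-Liquid, Results)

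**Not in the article, so assumed**
- Leaked mass: 50, 100 or 250 mg in total
- Puffs per session: 10 or 36 (36 is the number of puffs per bench experiment, borrowed here only as an upper value)

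**1. Reproduce the stated dose per puff.** 25.4 mg/m³ × 55 mL = 1.397 µg and 3.4 mg/m³ × 55 mL = 0.187 µg. These match 1.4 (SD 0.2) µg.

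**2. Liquid per puff.** 1.4 µg / 0.0002 = 7,000 µg = 7 mg. Each 7 mg leaked is therefore booked as one extra puff, or 1.4 µg of DEHP-d4.

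**3. Overstatement of total dose from a leak.** Overstatement = leaked mass / (8 × puffs per session × 7 mg).

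| Puffs per session (assumed) | Liquid truly puffed | DEHP-d4 truly puffed | 50 mg leak | 100 mg leak | 250 mg leak |
|---|---|---|---|---|---|
| 10 | 560 mg | 112 µg | 8.9% | 17.9% | 44.6% |
| 36 | 2,016 mg | 403 µg | 2.5% | 5.0% | 12.4% |

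A fraction with this dose in the denominator shrinks accordingly: 1/1.025 = 0.98 of its true value at the low end and 1/1.446 = 0.69 at the high end.

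**4. Concentration.** If the full 10% were lost before use, applying the nominal 0.02% overstates the dose by 1/0.90 − 1 = 11%. This multiplies the leak factor. It is an upper limit, because liquid used early in the week would have lost less and the decline may be analytical error.

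**5. Dose per session.** One total cannot give eight doses without assuming equal sessions. If session doses vary with coefficient of variation c (assumed), assigning each session one eighth of the total leaves a relative error of c × √(7/8): 13% for c = 14%, 28% for c = 30%, 47% for c = 50%.

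**The case against.** The strongest reply is that the article condenses a longer protocol. Puff logs, starting device weights or leak records may be in that document, so their absence here is not an error. That stands. The point rests on what the article does state: the weighing gives an exact amount, and a leak occurred.

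Second, the article does not give the size of the leak, so materiality is not established. That also stands, and is why the result is a range over labelled assumptions. The 7 mg per puff also assumes that 1.4 µg is all the DEHP-d4 aerosolized. If it is trapped mass uncorrected for 89% recovery, liquid per puff is 1.4 / 0.89 / 0.0002 = 7.9 mg, and every leak percentage falls by a factor of 0.89. The conclusion does not change.

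Third, a reader might infer more than the documents support:
- *Liquid left in the device is counted as puffed.* On the plain reading both device and vial are weighed on return, so retained liquid is on the balance.
- *The 89% impinger recovery means 11% stays in the device.* Its denominator is mass already aerosolized, so the shortfall may simply be trapping efficiency. It is no basis for correcting a participant's dose.
- *The mass balance of 100% (SD 22%; n=4) bounds the dose error.* It describes closure of a bench assay, not the error of a weighing.
- *Every planned rate estimate is compromised.* A log-linear elimination slope needs no dose. The Statistical Analysis section names absorption and elimination rates, not absorbed fraction.
- *The bench dose per puff is misused for participants.* The article does not propose it as their dose. It is used above only for scale.

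**Conclusion.** The point holds in this form. The weighing gives an estimated total, not an exact dose. As written, the rule books leaked liquid as inhaled DEHP-d4, and the article itself reports a leak. Under the assumed 50 to 250 mg leaked and 10 to 36 puffs per session over eight sessions, total dose is overstated by about 2.5% to 45%. A full 10% concentration loss would inflate it by up to a further 11%. The weighing alone gives no dose per exposure.

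The consequence is confined to dose-normalised results, to any modelling of the repeated exposures that uses dose, and to relating external to internal exposure. The true size for any participant is unknown, because neither the leaked mass nor the puffs per session are reported.

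**What to change.** Replace the word exact with estimated total under Participant Exposure, and say that the figure includes any liquid leaked and not measured.

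For participants not yet exposed:
- Weigh the device and the vial at hand-out, after the supervised day-1 exposure, at the existing day-3 visit and on day 5.
- Carry the device in a pre-weighed sealed bag, so that leakage in transit is measured and subtracted. Have any visible leak at home noted in the diary.
- Have participants log puffs and clock time per session, and apportion the weighed total by puffs.

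For the analysis:
- Report any dose-normalised result with and without participant 1.
- Give the dose as a range, from the nominal 0.02% to a concentration 10% lower.

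The cost is a few balance readings, a bag and a short diary, with most weighings at visits that already take place. The downside is a dose reported with uncertainty. The changes cannot repair data already collected: 5 of at most 10 participants were enrolled by May 2023. For those already exposed, only the wording, the dose range and the sensitivity analysis are available.

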#### Statistical Analysis

Standard descriptive statistics (ie, scatter plots, box plots, means, and SD) will be performed to describe the within-participant evolution of parent compound and metabolite distribution and elimination over time. Absorption and elimination rates will be estimated for each of the participants using standard nonlinear regression methods (hockey plots, piecewise linear regression models, or exponential models). These rates will be compared while accounting for potential effect modifiers (eg, age and gender) using mixed models.

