Children and adults living in industrialized countries are estimated to spend around 17-19 hours and 21 hours per day indoors (ie, at home and in the working environment), respectively [26]. There is considerable concern regarding phthalate exposures because several epidemiological studies have shown associations between exposures to some phthalates and retarded male reproductive development [11,12], altered semen quality [13,14], endometriosis [27,28], and respiratory diseases in children [29]. When inhaled, phthalates can reach the alveoli, be absorbed into the blood, and then be distributed to potential target tissues, where they may trigger an effect. Therefore, absorption rates (ie, rate at which the molecule enters blood), internal doses (ie, parent compound concentrations in blood), as well as metabolic and elimination rates (ie, rate of metabolites’ formation and elimination, usually in urine), are important toxicokinetic parameters to accurately determine the total exposures in the human body and, thus, potential risks to the population. Although urinary metabolite ratios were reported to be different between humans and animals [30-34], these toxicokinetic parameters have not been studied in humans exposed to phthalates through inhalation as a single exposure route. The few human toxicokinetic studies conducted with phthalates were mainly after ingestion [35-38]. A total of 2 human studies have been conducted on phthalates, including simultaneous exposure through the skin and inhalation routes [39,40]. These studies only provided estimated toxicokinetics (absorption, distribution, metabolism, and excretion [ADME]) for the inhalation route. Since inhalation is considered a significant indoor route of exposure for some phthalates [41], toxicological studies need to be performed to understand phthalates’ ADME through this exposure route. However, a procedure to expose healthy participants to SVOCs is lacking due to the absence of devices for human studies with SVOCs through inhalation. We aim to fill these gaps by describing the required steps to obtain human ADME data after inhalation. The SVOC selected in this study is DEHP, a model SVOC due to its major presence in the indoor environment (air and dust) and human populations (urine). This study is divided into 2 parts. Part I describes the dosing procedure and how to generate aerosols at environmentally relevant phthalate concentrations with a device suitable for chronic inhalation exposure. Airborne phthalate aerosols will be produced based on the technology of commercially available “electronic nicotine delivery systems” (ENDS), which have proven efficacy in generating aerosols for human use [42,43]. ENDS are generally used to generate nicotine or flavored aerosols from highly viscous liquids such as glycerol (viscosity=1412 mPa·seconds) making this technology suitable for viscous chemicals such as some phthalates. Part II provides the study protocol for participants exposed to ring-deuterated DEHP for several days. Unisanté has strong expertise in toxicological studies with healthy participants and has adapted its protocols for repeated, at-home exposure. We will show the results of the first participant here as proof of concept.

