#### Participant Timeline

The flowchart in Figure 3 shows the steps from participant screening and visits through exposure periods until data analysis. Briefly, an initial contact with the participant will be established by email to explain the study and obtain informed consent. Then, a phone call will be made to check if the inclusion and exclusion criteria are met and to get answers for a short general health questionnaire. If the inclusion criteria are met, the participant will be invited for a first visit. At this visit, the participant will sign the written informed consent. Women of reproductive age will also undergo a pregnancy test. Then, the participant will be given an aerosol-forming device and, after being instructed on how to use the device, will undergo the first inhalation exposure under the supervision of a research team member (see “Participant Exposure” section). A blood and urine sample will be collected before the first exposure (baseline) and will serve as baseline concentrations (control). Blood will be drawn again 30 minutes after the first exposure. Then, participants will follow the expected vaping schedule with DEHP-d4-spiked e-liquid and collect spot urine samples 4 times throughout the day (morning, midday, evening, and night) for the 4 days of exposure. Blood and urine collecting times are shown in Multimedia Appendix 1.

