## Appendix

Multimedia Appendix 1 Blood and urine sampling design. The exposure period is shown in grey. On day 1, blood and urine will be taken to provide baseline data (controls). Then, the first exposure starts and will be repeated twice a day, in the morning and in the evening. On day 3, participants return to our facilities to hand out day 1 to day 3 urine samples and for blood sampling. The last exposure is on day 4. On day 5, participants hand out urine samples from day 4 and the morning of day 5; a postexposure blood sample is collected at our facilities.

Multimedia Appendix 2 SCAHT_Experts_Outcome.

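### Individual absorption rates are to be fitted and compared by age and gender, but the blood sampling described is too sparse to identify them

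*Protocol article*

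**What the plan says.** The Statistical Analysis section of the protocol article fixes two steps. First, "Absorption and elimination rates will be estimated for each of the participants using standard nonlinear regression methods"; hockey-stick, piecewise linear and exponential curves are named as candidates. Second, "These rates will be compared while accounting for potential effect modifiers (eg, age and gender) using mixed models".

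The blood sampling is described in two places. Under Participant Timeline there is a baseline sample before any exposure, and then "Blood will be drawn again 30 minutes after the first exposure". Multimedia Appendix 1 adds: "On day 3, participants return to our facilities to hand out day 1 to day 3 urine samples and for blood sampling". It also says that on day 5 "a postexposure blood sample is collected at our facilities". The Abstract gives the exposure schedule as "2 short daily exposures over 4 days", which makes eight exposures.

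The Introduction defines absorption as entry of the molecule into blood. Spot urine is collected four times a day on the four exposure days, with a further sample on the morning of day 5. It is analysed for metabolites only. At most 10 participants are planned.

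**The concern.** Labelled compound is absent at baseline, so that sample carries no information on rates. Three informative blood occasions remain, and only one of them is tied to a stated interval after a known exposure. That interval is 30 minutes for every participant, so no contrast in early timing exists within or between people.

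The simplest usable model has three unknowns: absorption, elimination and a scale. Three values determine three unknowns exactly or badly, and leave nothing from which to judge the error.

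The second step then takes one fitted absorption rate per person, from at most 10 people, and relates it to age and gender. With one value per person, a participant random effect cannot be separated from residual error. A pattern by age or gender in such values could easily be a pattern in fitting error. The Introduction lists the absorption rate among the parameters not yet studied in humans for inhalation as a single route, so a misleading comparison would have little other evidence to correct it.

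**Working it through.** The article states no precision or sample-size figure, so there is nothing of its own to reproduce.

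**Step 1, count.** Non-baseline blood occasions: 30 minutes, day 3 and day 5, so 3. Unknowns: ka, ke and scale S (absorbed fraction × dose / volume), so 3. Residual degrees of freedom for one analyte in blood, with one draw per occasion: 3 − 3 = 0. This does not depend on any assumed kinetics.

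**Step 2, why the 30-minute value does not settle ka.** After one exposure,

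C(0.5)/S = ka/(ka − ke) × [exp(−0.5 ke) − exp(−0.5 ka)].

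With an assumed half-life of 5 h (ke = 0.139 per hour), this is 0.379 for ka = 1 and 0.607 for ka = 2. The same measured concentration therefore fits ka = 1 with scale S, or ka = 2 with scale 0.379/0.607 = 0.62 S. Between ka = 6 and ka = 10 the ratio moves only from 0.904 to 0.939.

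**Step 3, precision for one participant, blood only.** The model sums the one-exposure curve over eight exposures. Assumptions not in the article:
- exposures at 09:00 and 20:00;
- day 5 draw at 10:00;
- half-life 5, 10 or 15 h, and ka 0.7, 1.5 or 3 per hour;
- 25% error on the log scale.

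With J the derivatives of log C with respect to (log ka, log ke, log S), the information is JᵀJ/0.25², and SE(log ka) is the root of the first diagonal element of its inverse. The article gives no clock time for the day 3 draw, so it is varied:

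| Day 3 draw, time after morning exposure | SE(log ka) |
|---|---|
| 0.5 h | 2.2 to 92 |
| 1 h | 1.42 to 3.50 |
| 2 h | 0.79 to 1.61 |
| 3 h | 0.66 to 1.46 |
| 9 h | 0.92 to 2.84 |

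At 0.5 h the day 3 draw largely repeats the first one. At 3 h, the most favourable time in the table, the 95% range for one person's ka is a factor of exp(1.96 × 0.66) = 3.6 to exp(1.96 × 1.46) = 17 either way.

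**Step 4, against real differences.** With an assumed between-person SD of 0.30 in log ka, the share of variance in the fitted rates that is real is 0.30²/(0.30² + SE²):
- SE 0.66: 0.09/(0.09 + 0.436) = 17%.
- SE 1.46: 0.09/(0.09 + 2.132) = 4%.

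**Step 5, adding urine.** A second calculation used other assumptions: 15% error in blood, 30% in urine, 16 post-baseline urine samples, half-life 3 to 10 h, ka 0.5 to 6 per hour.
- SE(log ka) is 0.40 to 3.1 with the day 3 draw at 2 or 9 h, and 0.6 to 18 at 0.5 h. Even at 0.40 the real share is 0.09/(0.09 + 0.16) = 36%.
- SE(log ke) is 0.07 to 0.32 when ka is 1 per hour or more and the day 3 draw is at 2 or 9 h.

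Urine therefore supports elimination but does not rescue absorption.

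**Step 6, simulation.** Blood-only fits were simulated for 400 participants per scenario (half-life 5 h; ka 1, 2 or 6 per hour; 15% error; between-person SD 0.30 in log ka). The squared correlation of fitted with true log ka was 0.00 to 0.20. In the best scenario (typical ka 1 per hour) the fitted values ran from 0.27 to 2.7 per hour between the 5th and 95th percentiles.

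**The case against.** Several points on the other side are fair.

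- **Urine is not excluded.** The analysis text does not confine the fits to blood, so zero residual degrees of freedom applies only to a blood-only fit of one analyte. This stands as a limit, but Step 5 shows that adding urine leaves absorption poorly determined.
- **The sample count is inferred.** Multimedia Appendix 1 gives no number of draws for day 3, and the design figure is not shown. Three occasions are described; three samples is an inference. Several timed draws on day 3 would weaken the point.
- **The article is condensed.** It does not say that the second stage ignores estimation error, and exponential models can represent repeated exposures. Neither is a documented error. What is documented is the commitment to individual absorption rates and their comparison.

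A reader might also infer stronger claims that the documents do not support:

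- That all the individual rates, including elimination, are noise. The 16 to 17 timed urine samples per person can support elimination.
- That the uncertainty is always at least 16-fold. That figure belongs to a day 3 draw 1 h after exposure (exp(1.96 × 1.42) = 16); at 3 h it can be 3.6-fold.
- That absorption is the study's one main aim. The stated objective is method development to characterise absorption, distribution, metabolism and excretion together.

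**Conclusion.** The point holds for the absorption rate. As described, the blood sampling cannot give individual absorption rates precise enough to compare by age or gender. In every scenario examined, the fitting error exceeds the assumed between-person SD of 0.30: about 0.7 to 1.5 with the day 3 draw at 3 h, 1.4 to 3.5 at 1 h, and at least 0.40 under the more favourable error assumptions with urine added.

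The sizes rest on assumed kinetics, assay error and draw times. The count of three unknowns against three occasions does not, provided each occasion is one draw. The Blood and Urine Analysis section and the Discussion also disagree on whether the parent compound is measured in blood, and should be reconciled. If only metabolites are measured, uptake is further confounded with metabolite formation.

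This should be fixed before analysis. It does not undermine the descriptive results or the elimination rates.

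**What to change.** **Analysis.** Replace the two-stage analysis of absorption by one nonlinear mixed-effects model, fitted jointly to all participants' time-stamped blood and urine data, with the recorded exposure times and doses as input. Report the population absorption rate with its uncertainty, and show age and gender patterns descriptively only.

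The cost is more modelling work, and there would be no individual absorption rates to report as stand-alone results. The article describes weighing the device and vial on day 5, which gives a total. Unless the full protocol records each exposure, that total has to be apportioned over the eight.

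**Optional, for participants not yet studied.** Five had been enrolled by May 2023, so up to five remain. Vary the time of the single day 1 post-exposure draw among them instead of using 30 minutes for all. This takes no extra blood, but needs an amendment and a longer visit for some.

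The gain depends on the day 3 draw time. With 10 participants and five draws spread from 10 minutes to 4 h, the pooled SE(log ka) falls from 0.45–1.11 to 0.27–0.34 if the day 3 draw is at 1 h, but only from 0.21–0.46 to 0.20–0.30 at 3 h. These pooled figures use the Step 3 assumptions, are blood-only and allow for no between-person variance (for example 1.42/√10 = 0.45), so they are optimistic.
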